## Background

After successful cardiopulmonary resuscitation, 64 to 74% of patients remain unconscious at hospital arrival as a result of diffuse postanoxic encephalopathy [1, 2]. In these patients, a spectrum of electroencephalographic (EEG) changes can be observed, reflecting varying extents of ischemic brain injury [3]. Electroencephalographic status epilepticus is described in 10 to 35% [3–8] and is strongly associated with poor outcome: case fatality was 90 to 100% in prospective case series, despite treatment with anticonvulsants [4, 6–10]. Without EEG monitoring, approximately one in five cases remains undiscovered due to the absence of clinical signs [6, 11, 12].

The diagnostic criteria for electroencephalographic status epilepticus in comatose patients with postanoxic encephalopathy are controversial [13, 14]. The American Clinical Neurophysiology Society defines unequivocal seizures as generalized spike-wave discharges at 3 Hz or faster or clearly evolving discharges of any type at 4 Hz or faster, either focal or generalized [15]. However, some experts also consider other rhythmic or periodic patterns, such as generalized or lateralized periodic discharges or rhythmic delta activity as seizure activity [6, 8].

It is unclear whether electroencephalographic seizure patterns in patients with postanoxic encephalopathy represent a condition which can be treated with anticonvulsants to improve patients’ outcome, or have to be regarded as an expression of severe ischemic damage, in which treatment with anticonvulsants would be futile [16, 17]. Case series suggest that in patients with electroencephalographic status epilepticus, preserved brainstem reactions and EEG background reactivity are associated with a favorable outcome [4]. It is unclear whether treatment with anticonvulsants reduces the risk of a poor outcome in these patients and if so, how intensive this treatment should be. In the only prospective, non-randomized intervention study, a stepwise treatment up to pentobarbital-induced burst suppression resulted in a good outcome for 6% of patients with clinically overt or electroencephalographic status epilepticus [18]. This proportion is approximately the same as reported in observational studies, irrespective of treatment [4, 6, 8, 9].

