### Treatment allocation

All participating subjects receive standard best medical management according to current guidelines, including therapeutic hypothermia or controlled normothermia with sedation for 24 hours. In addition, they will be randomly assigned to either medical treatment or no treatment of electroencephalographic status epilepticus. In both groups, decisions regarding limitation or withdrawal of treatment will be made in accordance with the Dutch guidelines for postanoxic coma management [24]. Reasons for withdrawal of treatment will be documented.

Subjects will be randomized using ALEA (Clinical Trial Center Maastricht, The Netherlands), which is an online, central randomization service. To prevent imbalance of allocated treatments, blocked randomization will be used, with a 1:1 allocation, stratified by center, and random block size ranging from 4 to 10 subjects.

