### Statistical considerations

The primary analysis will be a single comparison between the treatment groups with regard to the primary outcome measure at 3 months, according to the intention-to-treat principle. To assess the effect of treatment with anticonvulsants, the absolute risk reduction of poor outcome will be calculated, including the corresponding 95% confidence interval. Baseline characteristics, raw distributions of the CPC score, and scores of secondary outcome measures will first be presented in a descriptive way. For secondary outcome measures, between-group differences will be analyzed by means of independent samples *t*-tests, Mann–Whitney tests, or Fisher exact tests, where appropriate. If necessary, multivariate regression analysis will be used to adjust for imbalances in main prognostic variables between the intervention and control groups.

Power calculations are hampered by the absence of data from randomized trials. With a presumed reduction of poor outcome from 99% to 92%, alpha of 5%, power of 80%, and 1-tailed testing, 84 patients per treatment group are needed to detect superiority of treatment with anticonvulsants. An O’Brien Fleming interim analysis will be performed after a total of 86 enrollments. If the difference between the treatment groups at that time is significant at *P* <0.00557, the trial will be stopped because of ‘proof beyond reasonable doubt’ that treatment with anticonvulsants is superior to treatment without anticonvulsants. To compensate for this interim analysis, two additional patients per group will be included. This indicates an intended sample size of 172 subjects.

With an estimated incidence of electroencephalographic status epilepticus of 20% in comatose patients with postanoxic encephalopathy [3], 860 patients will have to be monitored with continuous EEG. With five Dutch hospitals participating at the submission of this manuscript, we estimate an enrollment period of four and a half years.

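### One-tailed alpha of 5% and 80% power are stated together for 84 (then 86) per group, but no standard test checked delivers both; a test that holds 5% has about 76% power at best

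*Protocol article*

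**What the plan says.** All figures are in the protocol article, Statistical considerations, unless another section is named.

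- Effect: "With a presumed reduction of poor outcome from 99% to 92"%, that is, good outcome in 1% of controls and 8% of treated patients.
- Error rates and size: "alpha of 5%, power of 80%, and 1-tailed testing, 84 patients per treatment group are needed".
- Allocation (Treatment allocation): "blocked randomization will be used, with a 1:1 allocation", stratified by center with random blocks of 4 to 10.
- Interim: "An O’Brien Fleming interim analysis will be performed after a total of 86 enrollments", with early stopping for superiority at P < 0.00557.
- Adjustment for the interim: "two additional patients per group will be included", then "This indicates an intended sample size of 172 subjects", hence 86 per group.
- Primary analysis: a single intention-to-treat comparison, reported as an absolute risk reduction with a 95% confidence interval. No test is named for it.

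The Background gives a good outcome in 6% of patients in a non-randomized intervention study and adds: "This proportion is approximately the same as reported in observational studies, irrespective of treatment".

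**The concern.** Alpha, power and sample size are stated as one package. With 1% good outcome in one arm and 8% in the other, the final table will hold only a handful of good outcomes, and large-sample tests can then miss their nominal level. If the test that produces 84 exceeds 5% at plausible outcome rates, part of its 80% power comes from that excess. If the analysis uses a test that does hold 5%, the power is not 80%. In both cases the stated pair is not what the trial delivers. A null result would be read as coming from a better-powered trial than it was, and a borderline table such as 5 versus 1 would be positive under one test and negative under another.

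**Working it through.** **Inputs.** Good outcome 1% (control) and 8% (treated), one-sided 5%, 84 or 86 per group, and an interim at 43 per group with P < 0.00557, all from Statistical considerations. The 6% common rate is from the Background.

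**Step 1. Reproduce 84.** The usual closed-form formula with pooled variance is

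n = [1.645·√(2·0.045·0.955) + 0.842·√(0.01·0.99 + 0.08·0.92)]² / 0.07² = (0.4822 + 0.2432)² / 0.0049 = 107.4, so 108.

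Other closed forms give 106 (unpooled), 89 (arcsine) and 135 (continuity-corrected). None gives 84.

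Exact power does. For x control and y treated good outcomes, take

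z = [(y − x)/n] / √[p̄(1 − p̄)·2/n], with p̄ = (x + y)/(2n),

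reject if z ≥ 1.645, and sum Bin(x; n, 0.01)·Bin(y; n, 0.08) over the rejected tables. Power is 79.7% at 83, **80.15% at 84** and 80.9% at 86. From 70 per group upward, 84 is the first size to reach 80%. The unpooled z test gives the same result. The same calculation first reaches 80% at 124 for Fisher and Yates, 104 for Fisher mid-p and 81 for the arcsine test.

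**Step 2. Error rate of that test at 86 per group.** It rejects from 3 v 0, 5 v 1, 7 v 2, 9 v 3 and 10 v 4 (treated v control). The same sum with one common rate p in both arms gives:

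| Common good-outcome rate | 1% | 2% | 3% | 3.4% | 4% | 5% | 6% | 8% |
|---|---|---|---|---|---|---|---|---|
| True one-sided error | 2.4% | 5.3% | 6.2% | 6.2% (maximum) | 6.1% | 5.8% | about 5.6% | 5.3% |

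**Step 3. Where the excess and the power come from.** For 5 v 1, p̄ = 6/172 and z = 0.04651/0.02798 = 1.662, just above 1.645. At p = 3.4% this single table has probability Bin(1; 86, 0.034)·Bin(5; 86, 0.034) = 1.5%. Without it the error would be 6.2 − 1.5 = 4.7%. Under the design alternative it has probability Bin(1; 86, 0.01)·Bin(5; 86, 0.08) = 4.9%. Without it power falls from 80.9% to 76.0%. The table that breaks the level also supplies the power above 76%.

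**Step 4. Add the interim.** Enumerate 43 then 86 per group with the first look at P < 0.00557.

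- Final boundary from alpha spending (z = 1.6621, one-sided 0.0482): 5 v 1 (z = 1.6622) still counts. Maximum error 6.2%, power 81.0%.
- Classical O'Brien-Fleming final boundary (about 1.678): 5 v 1 drops out. Error is no more than 5.0% at common rates up to 10%, power 76%.

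**Step 5. Slightly unequal arms.** Uncorrected z test, common rates up to 10%, control/treated:

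| Arms | 84/88 | 85/87 | 86/86 | 87/85 | 88/84 |
|---|---|---|---|---|---|
| Maximum error | 5.2% | 5.1% | 6.2% | 5.9% | 5.6% |
| Power | 75.5% | 76.9% | 80.9% | 80.1% | 79.3% |

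**Step 6. Tests that hold one-sided 5%, 1% v 8%.**

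| Test | Power at 84 | Power at 86 |
|---|---|---|
| Exact unconditional, pooled z ordering (critical z about 1.69, maximum error 4.99%) | 75.0% | 76.0% |
| Boschloo | 69.8% | 70.9% |
| Fisher | 59.6% | 61.3% |

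Reading superiority from the 95% interval (z ≥ 1.96) holds the error to 2.8% at most, with power of 63.1% (pooled) or 65.2% (unpooled) at 86. A limited search over tailor-made rejection regions that hold 5% reached 76.3%.

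**The case against.** The strongest reply is that the article names no primary test. The uncorrected z test is inferred because it reproduces 84; planning a sample size with one test does not bind the analysis to it, and naming the test is properly left to an analysis plan that is not shown. This stands. A reader might infer that the trial's planned test has a 6.2% false-positive rate, and the documents do not support that. They commit to no such test, and at the design's own 1% rate the error is 2.4%. The 6.2% needs a common rate near 3.4%, which the protocol never states, and exactly equal arms, which stratified blocks across centers do not guarantee. It also turns on one table that clears the spending boundary by about 0.0001 in z. The 6% in the Background comes from a non-randomized series mixing clinically overt and electroencephalographic status epilepticus, and at 6% the error is about 5.6%.

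A reader might also infer that 84 is an arithmetic slip, because the common formula gives 108. It is not: exact power reproduces it.

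These replies do not rescue the stated pair. Each reading that removes the excess lowers the power: 63-65% with the 95% interval, 76% with the classical final boundary, 61% with Fisher (which the article lists only for secondary outcomes). An excess of about one point is ordinary for a large-sample test on sparse counts, and the article itself says its power calculation is hampered by lack of randomized data. That limits the weight of the point without making the figures consistent.

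**Conclusion.** The point holds in limited form. For 99% versus 92% poor outcome, no standard test checked gives both a one-tailed error of at most 5% and 80% power at 84 or 86 per group. Either the error reaches about 5.6% at the Background's 6% rate and at most 6.2%, with power of 80-81%, or the error is held and power is about 76% at best and 61% with Fisher. The calculation assumes independent binomial outcomes, the stated 1% and 8% rates, complete data and, except where shown, exactly 86 per arm. That the uncorrected z test lies behind 84 is an inference from the match. The shortfall in power does not depend on that inference; the size of the excess error does. The unnamed test is not itself a fault, and the choice of one-tailed testing is not at issue here. The statement should be corrected, but the design does not fail because of it.

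**What to change.** Settle the primary test before any outcome comparison is seen, choosing one that holds the stated one-sided 5%: for example, an exact unconditional test with pooled z ordering. Set its final-look level to be consistent with the interim boundary of P < 0.00557. State the power at 86 per group for that test, about 76% for the exact unconditional test, in place of 80%.

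The way the final level is set matters a little. If both looks are calibrated together by the enumeration in Step 4, the final critical z is about 1.70, the maximum error 4.9% and power stays at 76.0%. If the final exact test is simply run at 0.0482, power is about 74%. Under the jointly calibrated rule, 3 v 0 (z = 1.747) still counts as superiority and 5 v 1 (z = 1.662) does not.

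The cost is two sentences and a stated power 4 to 5 points less favourable (80 − 76 = 4 against the stated figure; 80.9 − 76.0 = 4.9 against the uncorrected test at 86). No patients are added and no trial procedure changes.

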### Safety assessments

Medical treatment of electroencephalographic status epilepticus may lower the high risk of death. The risk of an increase of morbidity or mortality is considered negligible. Otherwise, treatment may lead to prolonged hospitalization of several days of comatose patients who otherwise would have died. We assume this reasonable, since both antiepileptic treatment and no treatment are current standard modalities in these patients.

All adverse events reported by the investigator, staff, or spontaneously by the subject will be recorded in the electronic case record form. Adverse events are defined as any undesirable experience occurring to a subject during the clinical trial. A serious adverse event is defined as any adverse event that results in death, a life-threatening condition, inpatient hospitalization or prolongation of existing hospitalization, or persistent or significant disability.

The trial is monitored by an independent Data Safety Monitoring Board (DSMB). The DSMB is chaired by a biostatistician and further includes an intensivist and a neurologist. This committee will review data for safety after every 43 enrolled patients from the study have had their primary outcome measurement. Because of the expected high proportion of patients with a poor outcome in the study population, and the consequent overlap between safety endpoints and the primary endpoint, the evaluation of safety by the DSMB at that time will be qualitative. Summary of key efficacy endpoints (primary outcomes, mortality) will be provided for a planned interim analysis after 86 enrollments.

### Ethical approval

TELSTAR has received ethical approval from the Medical Research Ethics Committee Twente (Dutch: METC Twente) in December 2013 (reference: NL46296.044.13).

### Publication of trial results

The trial results will be published by the members of the Executive Committee, on behalf of the TELSTAR study team. With 36 or more enrollments, local principle investigators of participating centers will be included in the primary author list. Before submission of any manuscript, all local principal investigators will have had the opportunity to comment on the manuscript.

## Discussion

We present a study protocol for a multicenter, randomized controlled trial to investigate treatment of electroencephalographic status epilepticus in patients with postanoxic encephalopathy after cardiopulmonary resuscitation. Both sides of the spectrum, for example, antiepileptic treatment to burst suppression and no treatment at all of electroencephalographic status epilepticus are current standard modalities in these patients [19, 21]. The benefits of antiepileptic treatment have never been investigated in a randomized controlled trial.

The focus of debate is often whether EEG patterns represent epileptic activity, that can be treated with anticonvulsants to improve outcome, or not [13, 14]. In the only prospective case series of intensive antiepileptic treatment in these patients, EEG patterns of enrolled subjects were insufficiently reported [18]. In the current trial, we include a broad range of possibly epileptiform EEG patterns. However, with a clear definition of the distinct eligible seizure patterns, based on standardized EEG terminology [15], we aim to increase insight into the effects of treatment in relation to specific patterns. Although EEG analysis prior to patient enrollment will be performed locally by the treating neurologist or clinical neurophysiologist, all EEGs will also be analyzed off-line by dedicated clinical neurophysiologists, to optimize categorization of patterns.

If beneficial at all, the optimal duration of treatment of status epilepticus in postanoxic encephalopathy is unclear. Previous studies suggest that in more than half of cases the duration of seizure activity is less than 24 hours, and in more than three quarters of cases less than 48 hours [5, 12]. We consider ongoing status epilepticus after suppression of all epileptiform activity for 2 × 24 hours as refractory and argue that patients with ongoing seizure activity beyond this period are unlikely to benefit from prolonged antiepileptic treatment.

In previous, non-randomized studies concerning treatment of status epilepticus after cardiopulmonary resuscitation, diagnosis was either based on clinical signs [29–31], or EEG seizure activity [6, 8, 10], or a combination of clinical and EEG findings [4, 18]. However, myoclonic jerks are often suppressed by sedative medication. Furthermore, myoclonia are often unrelated to EEG findings. For most neurologists, the threshold to treat patients with overt myoclonia is lower than for patients with non-convulsive electroencephalographic seizures. However, irreversible damage is probably even more likely in patients with myoclonia, since the risk of poor outcome is larger [4] and neuronal necrosis is more common [17]. In the current study, the diagnosis of status epilepticus is EEG-based, irrespective of clinical signs.

Our study protocol intends to minimize time from onset of electroencephalographic status epilepticus to start of treatment, as ongoing seizure activity may lead to additional damage [22] and decreased effect of medication [23]. EEG monitoring will be started within 24 hours. Epileptic activity that is initially suppressed by the anticonvulsive effects of hypothermia and sedative medication will therefore be detected early. The maximum time of 3 hours since the diagnosis to obtain informed consent and commence treatment is chosen pragmatically.

Although the trial protocol contains clear recommendations, including the intensity of antiepileptic treatment in the intervention group, the diagnosis of electrographic status epilepticus and the choice of specific anticonvulsive medication are ultimately left to the discretion of the treating physician. Since we consider the pragmatic character of this difficult trial very important, we accept potentially detrimental effects of variations due to freedom of treatment. These include restricted extrapolation resulting from differences between local protocols and effect dilution resulting from treatment of overt myoclonia with anticonvulsants in the control group.

Blinding of treating physicians for treatment allocation is virtually impossible, as the administration of anticonvulsants is guided by bedside EEG measurements. However, outcome assessment of surviving patients is performed blinded for the treatment allocation.

Concluding, this study will be the first to evaluate the additional value of medical treatment of electroencephalographic status epilepticus for patients after successful cardiopulmonary resuscitation. Furthermore, it will provide clinical and electrographic characteristics for identifying patients that might benefit from this treatment.

## Trial status

Recruitment to TELSTAR started in May 2014, with 5 participating hospitals. Interested centers with ICU and continuous EEG monitoring facilities are welcome to participate.

## Abbreviations

APACHE: Acute Physiology and Chronic Health Evaluation
CPC: Cerebral Performance Category
DSMB: Data Safety Monitoring Board
EEG: electroencephalography
MADRS: Montgomery and Åsberg Depression Rating Scale
PROBE: Prospective Randomized Open Blinded Endpoint
SF-36: Medical Outcomes Study 36-item short-form health survey
WMO: Dutch Medical Research Involving Human Subjects Act.
